## Abstract

**Background:**

Low levels of serum selenium are associated with increased risk of mortality among HIV+ patients in East Africa. We aim to assess the effect of selenium supplementation on CD4 cell count, HIV viral load, opportunistic infections, and quality of life in HIV-infected patients in Rwanda.

**Methods and Design:**

A 24-month, multi-centre, patient and provider-blinded, randomized, placebo-controlled clinical trial involving 300 pre-antiretroviral therapy (ART) HIV-infected patients will be carried out at two sites in Rwanda. Patients ≥ 21 years of age with documented HIV infection, CD4 cell count of 400-650 cells/mm^3^, and not yet on ART will be recruited. Patients will be randomized at each study site using a randomized block design to receive either the selenium micronutrient supplement or an identically appearing placebo taken once daily. The primary outcome is a composite of time from baseline to reduction of CD4 T lymphocyte count below 350 cells/mm^3^ (confirmed by two measures at least one week apart), or start of ART, or the emergence of a documented CDC-defined AIDS-defining illness. An intention-to-treat analysis will be conducted using stepwise regression and structural equation modeling.

**Discussion:**

Micronutrient interventions that aim to improve CD4 cell count, decrease opportunistic infections, decrease HIV viral load, and ultimately delay initiation of more costly ART may be beneficial, particularly in resource-constrained settings, such as sub-Saharan Africa. Additional trials are needed to determine if micro-supplementation can delay the need for more costly ART among HIV-infected patients. If shown to be effective, selenium supplementation may be of public health importance to HIV-infected populations, particularly in sub-Saharan Africa and other resource-constrained settings.

**Trial Registration:**

NCT01327755

## Background

In sub-Saharan Africa, more than 30 million people are living with HIV/AIDS, malnutrition and food insecurity are endemic [1] HIV infection compromises the nutritional status of infected individuals and poor nutritional status can enhance progression of the disease [2]. The relationship between immune function and nutritional supplementation has been well described [3-6]. Studies have reported a high prevalence of nutrient deficiencies early in the course of HIV infection [7-9].

It is well understood that micronutrient deficiencies and HIV disease progression aggravate each other [10,11]. Among HIV-infected persons not receiving antiretroviral therapy (ART), observational studies have shown that low or deficient serum concentrations of several micronutrients are associated with low CD4 cell count, advanced HIV related diseases, faster disease progression, or HIV-related mortality [12-26]. Selenium is one essential nutrient necessary for endogenous antioxidant defense. Selenium deficiency, as indicated by low plasma selenium concentrations, is common among HIV-infected individuals [27,28].

While many observational studies on selenium in HIV-infected patients have been conducted in developed countries over the past decade, few have been conducted in sub-Saharan Africa. Clinical trial data on selenium supplementation is also limited in both developed and developing countries. There are two recent high-impact randomized clinical trials (RCTs) that have been conducted to assess the individual association of selenium supplementation on HIV viral load and CD4 cell count. The first trial, conducted in Miami by Hurwitz et al [29], found that selenium supplementation of 200 μg daily significantly suppressed the progression of HIV viral load and improved CD4 cell count after 9 months of treatment. The second trial, conducted in Tanzania by Kupka et al [30], found that selenium supplementation of 200 μg daily provided to HIV-infected pregnant women before and after pregnancy (between 12 and 27 weeks of gestation and 6 months after birth) had no significant effect on HIV viral load or CD4 cell count, but did significantly lower risk of infant death.

Although the results of these two clinical trials appear to contradict, it is important to recognize the inherent differences in their design, setting, and populations under study. Additional evidence from other settings and populations is still required to more accurately determine the effect of selenium supplementation on HIV viral load and CD4 cell count in HIV-infected individuals. Therefore, we have designed a randomized trial to examine the effect of selenium supplementation on CD4 cell counts in HIV-infected patients who are not yet on ART. This trial will take place in Rwanda, where an estimated 250,000 adults and children are living with HIV [31], of which only 50,000 are receiving ART [32].

### Registration

This trial has been registered with ClinicalTrials.gov. The registration number is NCT01327755.

### Study Design

This study is a 24-month, multi-centre, patient, provider and analyst-blinded, randomized, placebo-controlled clinical trial involving 300 pre-ART HIV-infected patients in Rwanda. (See Figure 1 for a study flow diagram.)

**Figure 1 F1:**
[figure not shown]
**Study flow diagram**. This figure displays the intended recruitment and measurement points in this trial.

### Objectives and Hypothesis

The primary outcome of the study is time from baseline to reduction of CD4 T lymphocyte count below 350 cells/mm^3^ (confirmed by two measures at least one week apart), or start of ART, or the emergence of a documented CDC-defined AIDS-defining illness. We hypothesize that selenium supplementation in pre-ART patients will improve CD4 cell counts, decrease opportunistic infections, decrease HIV viral load, and delay ART initiation.

### Setting and Participants

Patients will be recruited at two purposely-selected health facilities that offer care and treatment for HIV/AIDS patients in Rwanda. These facilities have been chosen due to the feasibility of recruiting all patients within a 3-4 month period and the feasibility of coordination.

Patient eligibility will be restricted to HIV-infected adults 21 years of age and older at study enrolment. Only patients not yet eligible for ART will be included. Only patients with CD4 cell count between 400 and 650 cells/mm^3 ^will be selected because they are at similar immunological level and hence they will not be eligible to start ART treatment at the start of the study. Eligible participants must also be willing to practice a barrier method of birth control at all times. Written informed consent will be required from patients to participate in this study.

Eligible patients will be identified from patient registers. These patients will be informed about the study during a regular scheduled clinic visit or through home visits by site staff not otherwise involved in data collection. Patients who are interested in the study will be provided with further details and consent procedures. Those fitting the inclusion criteria will be enrolled and followed for 2 years. Study assessments will occur at baseline, 6, 12, 18, and 24 months.

Patients will be excluded if they are intending to be transferred out of the clinic catchment area before study ends and/or if they are scheduled to start ART. Moribund patients, pregnant women, and those unable or not wanting to commit to barrier method of birth control will also be excluded.

### Randomization

Participants will be randomized using a simple randomized block design to receive either selenium or an identically appearing placebo to be taken once daily for 24 months. The Rwandan Ministry of Health recommends the use of co-trimoxazole, a sulfonamide antibiotic combination of trimethoprium and sulfamethoxazole used for the treatment of a variety of bacterial infections, for all HIV-infected patients. Therefore, all participants will also receive co-trimoxazole irrespective of experimental assignment. Participants who do not return to the clinic as scheduled will be followed up at home.

Study participants will be identified by a unique study identification number. The randomization schedule will be prepared by the product manufacturer, Seroyal, and the randomization sequence will be concealed from the study investigators and providers. Study participants will be assigned a specific allocation number. An unblinding list will be kept at the site of the manufacturer and will be provided as needed to the Data and Safety Monitoring Officer (DS). Site study personnel (investigator and clinical personnel monitoring the safety and laboratory assay results) and study participants will be blinded with respect to the allocation. Unblinding of an individual study participant will be indicated in the event of a medical emergency where the clinical management/medical treatment of the study participant could be altered by knowledge of the group assignment allocation of the investigational product.

### Intervention

The trial intervention will consist of capsules containing 200 mcg of selenium in the form of selenium yeast, which contains selenomethionine. Capsules will be provided in bottles of 30 (one months supply) and participants will be instructed to take one capsule daily. Selenium will be stored in a dry cool location during the course of the trial. Shelf life of the product is well beyond the two-year time period expected for the trial duration. To ensure optimal adherence, participants will receive adherence counseling at baseline and when picking up refills on a monthly basis. Additional adherence counseling will be provided to patients who have sub-optimal adherence.

Selenium capsules are supplied by Seroyal, a Canadian Nutraceutical company. The sponsors of the trial and the investigators will be responsible for ensuring that the investigational pharmaceutical product is safe. Comparator products (placebo) supplied for the clinical trial will be of proven quality and will be available to be verified by the National Bureau of Standards. Records will be kept of information about the shipment, delivery, receipt, storage, return, and destruction of any remaining pharmaceutical products. The investigators will not supply the investigational product to any person not targeted to receive it.

### Outcomes

The primary outcome of the study is a composite outcome involving reduction of CD4 T lymphocyte count to below 350 cells/mm^3^ (confirmed by two measures at least one week apart), or start of ART, or the emergence of a documented CDC-defined AIDS-defining illness. Secondary outcomes includes viral suppression at 6, 12, 18, and 24 months; quality of life; weight gain; presence of opportunistic infections and mortality.

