#### HIV Viral Load and CD4 Cell Count

At baseline, and at month 6, 12, 18 and 24, blood draws will be done for assessment of CD4 cell count and HIV viral load. Blood samples will be collected into EDTA tubes (Becton Dickinson, San Jose, CA, USA). The viral load samples will be transported and analyzed at the National Reference Laboratory within 4 hours; plasma will be separated from cells by centrifugation at 200 g, aliquoted and stored at -70°C until the real time PCR will be performed using Cobas TaqMan 48 (Roche Diagnostic Systems, NJ, USA) that has a detection limit of 40 RNA copies/ml. The RNA will be extracted from the plasma with chloroform, followed by alcohol precipitation and dilution with the HIV Monitor specimen diluent (100 μl). Amplification and detection of the extracted RNA (40 μl) will be performed in accordance with the manufacturer's instructions. CD4 cell count will be measured at the National Reference Lab, or the site laboratory, using FACS Count (Becton Dickinson immunocytometry).

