### Analysis Plan

Analysis will be conducted jointly by the study team in Rwanda and in Canada using standard statistical software. The analysis and reporting of the results with follow the CONSORT guidelines [38]. The statistician/data analyst will be blinded to the study group. The process of patient selection and flow throughout the study will be summarized using a flow-diagram (See Figure 1). The analysis results of patient demographics and baseline outcome variables (both primary and secondary) will be summarized using descriptive summary measures: expressed as mean (standard deviation) or median (minimum-maximum) for continuous variables and number (percent) for categorical variables. We will adopt an intention-to-treat principle to analyze all outcomes, meaning that data from participants will be analyzed according to the group to which they were randomized even if they do not receive the allocated intervention. We will also use multiple-imputation to handle missing data. We will use the T-test for comparing groups on continuous outcomes and the chi-squared test for binary outcomes. We will consider a threshold of 0.05 as statistical significance. For all group comparisons, the results will be expressed as effect (risk ratio for binary outcomes), corresponding two-sided 95% confidence intervals and associated p-values. P-values will be reported to three decimal places with values less than 0.001 reported as < 0.001. Because the primary outcome is a composite outcome, we will assess heterogeneity between the included outcomes [39,40]. Further, adjusted analyses using the following baseline covariates (age, gender, nutritional status) will be performed using regression techniques to investigate the residual impact of key baseline characteristics on the outcomes. Goodness-of-fit will be assessed by examining the residuals for model assumptions and chi-squared test of goodness-of-fit. All analyses will be performed by a professional statistician.

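### Viral suppression, compared by randomised group in patients who enter off ART, will largely reflect who started ART and is pushed against selenium if selenium delays ART

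*Protocol article*

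**What the plan says.** All places are in the protocol article.

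- **Outcomes:** "Secondary outcomes includes viral suppression at 6, 12, 18, and 24 months". No other secondary outcome concerns the virus. No threshold is given.
- **Setting and Participants:** "Only patients not yet eligible for ART will be included", and "Those fitting the inclusion criteria will be enrolled and followed for 2 years". No stop or separate handling at ART start is stated.
- **Outcomes, primary composite:** besides a confirmed CD4 fall, the events are "or start of ART, or the emergence of a documented CDC-defined AIDS-defining illness". ART start is thus expected during follow-up.
- **Objectives and Hypothesis:** selenium is expected to "decrease opportunistic infections, decrease HIV viral load, and delay ART initiation".
- **HIV Viral Load and CD4 Cell Count:** viral load is measured at baseline and at all four later visits, by an assay that "has a detection limit of 40 RNA copies/ml".
- **Analysis Plan:** "We will adopt an intention-to-treat principle to analyze all outcomes". Binary outcomes get a chi-squared test and a risk ratio, continuous outcomes a t-test. The listed adjustment covariates are age, gender and nutritional status, all at baseline.

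**The concern.** Two hoped-for effects of selenium, lower viral load and later ART, act on this outcome in opposite directions. ART is the main route to suppression in a population that enters untreated. If selenium slows progression, fewer selenium patients will be on ART at a given visit, and fewer will be suppressed for that reason alone. The arm that does worse clinically can look better virologically.

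Two things are at stake. First, a favourable primary result could be accompanied by a viral result that appears to contradict it. Second, the question about selenium and viral load would go largely unanswered, because a proportion suppressed by randomised group mixes any selenium effect with the effect of differential ART.

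**Working it through.** The article states no figure for this outcome, so there is none to reproduce. The check asks how far differential ART start alone would move the comparison.

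**Inputs from the article**
- Control event rate 60% at one year (Sample Size Calculation). This is a CD4-depletion rate, not an ART rate.
- Relative risk reduction of about 25%, so 0.60 × 0.75 = 0.45 on selenium. Table 1 prints 44%; 45% is used here.
- 300 patients in total, two-sided 5% level.

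**Assumptions, not in the article**
- 1:1 allocation, so 150 per arm.
- f, the share of primary events on ART at the visit: 0.25 to 1.
- s, suppression on ART: 0.70 to 0.90.
- q, suppression off ART: 0 to 0.10, equal in both arms (no direct viral effect).

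**Formulas**
- Share on ART: a = f × 0.60 (placebo), f × 0.45 (selenium).
- Proportion suppressed: p = a·s + (1 − a)·q.
- Share of suppressed placebo patients who are on ART: a·s / p.
- Off-ART suppression that selenium needs in order to tie: (p_placebo − a_selenium·s) / (1 − a_selenium).
- Chance of a significant wrong-direction result: two-proportion power at 150 per arm.

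With q = 0 the risk ratio is (f × 0.45 × s) / (f × 0.60 × s) = 0.75, whatever f and s are.

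**Worked cases**
- f = 1, s = 0.80, q = 0.01. Placebo: 0.60 × 0.80 + 0.40 × 0.01 = 0.484. Selenium: 0.45 × 0.80 + 0.55 × 0.01 = 0.3655. Risk ratio 0.76; chance of a significant reversal 55%.
- f = 0.5, same s and q. Placebo: 0.30 × 0.80 + 0.70 × 0.01 = 0.247. Selenium: 0.225 × 0.80 + 0.775 × 0.01 = 0.188. Risk ratio 0.76; chance 24%.
- f = 0.25, s = 0.70, q = 0.10. Placebo: 0.15 × 0.70 + 0.85 × 0.10 = 0.190. Selenium: 0.1125 × 0.70 + 0.8875 × 0.10 = 0.1675. Risk ratio 0.88; chance 7%.

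**Whole range**

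| f | Risk ratio | Suppressed placebo patients who are on ART | Chance of significant reversal |
|---|---|---|---|
| 0.25 | 0.75-0.88 | 55-100% | 7-15% |
| 0.50 | 0.75-0.84 | 75-100% | 14-28% |
| 0.75 | 0.75-0.82 | 85-100% | 23-45% |
| 1.00 | 0.75-0.80 | 91-100% | 35-65% |

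**Break-even.** With 1% suppressed off ART on placebo, selenium must reach 3.9% off ART merely to tie at f = 0.25, s = 0.70: (0.1135 − 0.07875) / 0.8875. At f = 1, s = 0.90 it must reach 25.3%: (0.544 − 0.405) / 0.55.

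In every case the risk ratio is below 1, and most suppressed placebo patients are on ART. The direction is stable; the size is not.

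**The case against.** The strongest points on the other side are these.

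- **The outcome is not defined as yes/no at 40 copies/ml.** This stands. The figure is only the assay's limit, and the Background section uses the verb suppress for a quantitative effect. A reader might infer a 40-copy threshold; the article does not set one. The concern does not depend on it. If suppression means lower viral load, a comparison across ART start is still driven by ART in the same direction. Only the mismatch with the hypothesised decrease depends on the yes/no reading, which is the usual one.
- **A condensed article may leave the handling of ART start to a fuller plan.** This stands as far as it goes, and neither the missing threshold nor the missing ART rule is the finding. But the outcome, its visits and comparison of all outcomes by randomised group are stated here, and a fuller plan that simply followed them would inherit the problem.
- **Not every primary event leads to ART.** This stands. A CD4 fall or an AIDS-defining illness counts without ART. The Sample Size Calculation section reports that East African patients start treatment at a median CD4 of 141 to 169, and the Background section reports 50,000 treated of 250,000 living with HIV. ART may lag well behind the event, so low values of f are credible.
- **Comparison regardless of ART start is a legitimate treatment-policy estimand.** True, and it is worth reporting. It answers what assignment to selenium does to viral load with ART use as it falls out, not whether selenium itself lowers viral load.
- **Selenium may act directly on the virus.** That is the hypothesis, and a large enough effect off ART would offset the push. The break-even figures show how large.

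**Conclusion.** The concern holds in this form: the comparison of viral suppression by randomised group is confounded by differential ART start, is pushed against selenium if selenium delays ART, and does not directly measure the hypothesised decrease in viral load. Under the assumed ranges and with no direct viral effect, the risk ratio is about 0.75-0.88 and the chance of a significant reversal about 7-65%. The push is weaker at early visits, when fewer patients will have started ART.

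A reader might go further and infer that an effective supplement would certainly look harmful, or take a figure near the top of the range as the expected risk. The documents do not support either. The upper values need every primary event to be on ART, the 60% is a CD4-depletion rate, and ART uptake and suppression rates are not given. The problem is confined to a secondary outcome; the primary outcome is unaffected.

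**What to change.** Before unblinding:

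1. Make the viral-load outcome the change from baseline in log10 viral load over visits before ART start, in a mixed model adjusted for baseline log10 viral load.
2. Add a sensitivity analysis for informative ART start, for example a composite ranking that places ART starters worst. This brings ART delay into the outcome, so it supports the main analysis and does not replace it.
3. Report suppression by ART status descriptively, alongside the all-visits comparison by randomised group, and state the threshold used.

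A binary outcome of suppression without ART should not be the main replacement. If few patients are suppressed off ART, it will be near zero in both arms and carry little information.

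**Cost.** No new data are needed, since viral load is already scheduled at baseline and all four later visits. The downside is that the pre-ART model relies on a missing-at-random assumption after ART start, which is doubtful because ART start is tied to progression; hence the sensitivity analysis.

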### Measurement of Outcomes and Other Variables of Interest

#### Patient Interviews

Trained nurses will use a structured questionnaire to collect data on patients' demographics at baseline. Additionally, at baseline and at each follow-up visit, a questionnaire will be used to collect information on psychosocial factors, access to care and treatment, attitudes towards and experiences with the supplementation, quality of life, self-efficacy, nutrition, opportunistic infections, and adherence to the study protocol. The questionnaire will be available in English and Kinyarwanda. Nurses will also use a data abstraction tool at baseline and at each follow-up visit to obtain information on height, weight, blood pressure and other clinically relevant information.

#### HIV Viral Load and CD4 Cell Count

At baseline, and at month 6, 12, 18 and 24, blood draws will be done for assessment of CD4 cell count and HIV viral load. Blood samples will be collected into EDTA tubes (Becton Dickinson, San Jose, CA, USA). The viral load samples will be transported and analyzed at the National Reference Laboratory within 4 hours; plasma will be separated from cells by centrifugation at 200 g, aliquoted and stored at -70°C until the real time PCR will be performed using Cobas TaqMan 48 (Roche Diagnostic Systems, NJ, USA) that has a detection limit of 40 RNA copies/ml. The RNA will be extracted from the plasma with chloroform, followed by alcohol precipitation and dilution with the HIV Monitor specimen diluent (100 μl). Amplification and detection of the extracted RNA (40 μl) will be performed in accordance with the manufacturer's instructions. CD4 cell count will be measured at the National Reference Lab, or the site laboratory, using FACS Count (Becton Dickinson immunocytometry).

### Sample Size Calculation

We chose our CD4 depletion event rate based on the work of the CASCADE cohort which displays an average CD4 depletion of 114 (32-229) cells/μl per year and where 54% of individuals had a decline > 100 cells/μl per year if CD4 evaluations were rare, as in Rwanda [33]. We expect that the majority of participants in our study, about 60%, will enter the study with a CD4 at risk of reaching 350 cells/μl within the first year as most evidence demonstrates that patients in East Africa initiate treatment due to symptomatic HIV with a median CD4 of 141 to 169 (depending on source). Thus, patients with a high CD4 will be somewhat more rare to enroll [34,35].

We applied several sample sizes to display that even small changes in the relative risk of the intervention will yield a large impact on the required sample size (see Table 1). Our three sample size assumptions are based on the likelihood of an intervention delivering a small, moderate or large effect (relative risk reduction of 10, 25, and 50%). Given that we do not have strong evidence from previously completed trials, we are assuming the event of depleting CD4 status will occur in 60% of control patients at one year and 60% of experimental patients at one year if the intervention delivers no effect. Table 1 provides the estimates required for power of 80% and an alpha of 0.05.

**Table 1 T1:** Sample Size Calculation estimates

RRR	Control event rate	Experimental event rate	Sample size	Power
10%	60%	55%	2312	80%
25%	60%	44%	314	80%
50%	60%	29%	76	80%

We employed several methods to make these calculations. The below estimates are based on Markov Chain Monte Carlo Methods whereby we explored the impact of adherence/retention to the intervention and examined the differing possible risks of an underlying disease event. We performed 5,000 simulations for each estimate. As we employ informed estimates, using a Bayesian profile, our estimates may differ slightly compared with other software approaches. However, they should not differ to an important amount.

Based on these calculations and our resources, we aim to enroll 300 patients in the trial. This leads to an RRR slightly lower than 25% and represents a very important reduction in events. Recognizing that no single trial can provide definitive evidence of effectiveness, this trial will contribute to the overall evidence of selenium supplementation for CD4 maintenance [36,37]. If control patients demonstrate lower rates of compliance to the intervention due to a lack of effects of, say, 20%, the power is increased to 96% and an alfa of 0.25. At the conclusion of our trial, we will conduct a meta-analysis to determine the overall power that current evidence contributes to answering this clinical question.

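### Table 1 is attributed to simulations of adherence and retention, but its 25% and 50% rows match the plain formula with no allowance for either, and enrolling 300 leaves no margin on the plan's one-year basis

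*Protocol article*

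**What the plan says.** All of this is in the protocol article. The Sample Size Calculation section sets the control rate: "we are assuming the event of depleting CD4 status will occur in 60% of control patients at one year". It considers three effects, a "relative risk reduction of 10, 25, and 50" per cent. "Table 1 provides the estimates required for power of 80% and an alpha of 0.05". The three rows are 60% v 55% (2312 patients), 60% v 44% (314) and 60% v 29% (76).

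On method it says: "The below estimates are based on Markov Chain Monte Carlo Methods whereby we explored the impact of adherence/retention to the intervention". It adds that the results should be close to those of other software. No adherence or retention rate is given, and Table 1 has no column for either.

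Enrolment is then fixed: "Based on these calculations and our resources, we aim to enroll 300 patients in the trial". The next sentence says that this corresponds to a relative reduction a little under 25%. The only adherence scenario reported is 20% lower compliance among controls, which is said to raise power.

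Elsewhere the article provides for home follow-up of missed visits (Randomization), extra counselling where adherence is poor (Intervention), and an intention-to-treat analysis (Analysis Plan) with this rule: "We will also use multiple-imputation to handle missing data".

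**The concern.** An allowance for loss raises the sample size above the complete-data figure. An allowance for non-adherence under intention-to-treat moves the experimental event rate towards the control rate, which also raises the sample size. If the simulations fed either into Table 1, the printed sizes or rates should show it.

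If they did not, the 80% in the table is a best-case figure, while the text suggests that the usual losses are built in. Readers could then place more weight on a null result than the stated calculation supports. The one compliance scenario that is reported favours the trial. Non-adherence on selenium, which works against it, is not quantified.

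**Working it through.** **Inputs.** Alpha 0.05 and power 80% come from the Sample Size Calculation section. I take the test as two-sided because the Analysis Plan promises "corresponding two-sided 95% confidence intervals and associated p-values". Event rates and sizes are those of Table 1, and enrolment is 300. I assume 1:1 allocation (150 per arm), since no ratio is stated.

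**Formulae**, with n per arm, d = p1 − p2, V = p1(1−p1) + p2(1−p2), and p̄ the mean rate:

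- Unpooled: n = (1.960 + 0.8416)² V / d²
- Pooled: n = [1.960√(2p̄(1−p̄)) + 0.8416√V]² / d²

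**Step 1: the 25% row (60% v 44%).** V = 0.24 + 0.2464 = 0.4864 and d² = 0.0256.

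- Unpooled: 7.849 × 0.4864 / 0.0256 = 149.1, so 150 per arm, 300 in total.
- Pooled: (1.960 × 0.7065 + 0.8416 × 0.6974)² / 0.0256 = 151.9, so 152 per arm, 304 in total.

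The printed 314 is 3-5% above these (314/304 = 1.033; 314/300 = 1.047). An unrounded rate of 44.26%, which prints as 44%, gives exactly 314 with the pooled formula. Continuity correction gives 330, above the printed figure.

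**Step 2: the 50% row (60% v 29%).** V = 0.4459 and d² = 0.0961. Unpooled: 36.4, so 74 in total. Pooled: 39.1, so 80 in total. Printed: 76.

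**Step 3: the 10% row.** The pooled total is 3068 for the printed 55%, and 2136 for 54%, the exact 10% reduction. The printed 2312 matches neither, so I draw nothing from this row.

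**Step 4: is dilution visible in the rates?** Undiluted rates are 0.75 × 60% = 45% and 0.50 × 60% = 30%. Non-adherence on selenium would push them up. Table 1 prints 44% and 29%, which are lower.

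**Step 5: power at 300 with no loss.** For 60% v 44%, √(V/150) = 0.0569 and √(2p̄(1−p̄)/150) = 0.0577.

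- Unpooled: Φ(0.16/0.0569 − 1.960) = Φ(0.850) = 80.2%.
- Pooled: Φ((0.16 − 1.960 × 0.0577)/0.0569) = Φ(0.824) = 79.5%.

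For 60% v 45%, the same formulae give 74.9% and 74.2%. The sample size needed there is 342-346.

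**Step 6: detectable reduction.** Solving for the experimental rate that gives 80% power at 300 yields 44.0% (unpooled) or 43.9% (pooled), a relative reduction of 26.6-26.8%. At 314 it is 26.0-26.2%. The printed 44% is itself a reduction of 1 − 44/60 = 26.7%. Going from 314 to 300 raises the detectable reduction; it cannot bring it below 25%.

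**Step 7: loss and non-adherence at 300.** The rates below are my assumptions. Loss reduces n. Non-adherers on selenium are given the control event rate, so 10% non-adherence turns 44% into 0.9 × 44 + 0.1 × 60 = 45.6%. Each range runs from pooled to unpooled.

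| Loss | Selenium non-adherence | Power, 60% v 44% | Power, 60% v 45% |
|---|---|---|---|
| 0 | 0 | 79.5-80.2% | 74.2-74.9% |
| 10% | 0 | 75.2-76.0% | 69.6-70.4% |
| 0 | 10% | 70.7-71.4% | 65.1-65.7% |
| 5% | 5% | 73.1-73.9% | 67.5-68.2% |
| 10% | 10% | 66.1-66.8% | 60.5-61.2% |
| 20% | 20% | 51.1-51.8% | 46.2-46.8% |

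**The case against.** **Exploring is not inflating.** The article says only that the simulations "whereby we explored the impact of adherence/retention to the intervention and examined the differing possible risks of an underlying disease event". It never says in terms that an allowance is included, and it tells readers to expect sizes close to those of standard software. The full protocol may list the inputs. This stands in part: leaving those inputs out of an article is not a fault. But the same sentence presents the Table 1 sizes as based on that work, and the printed results show no trace of it.

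**Rounding.** Rates from 43.5% to just under 44.5% all print as 44% and give pooled sizes from 286 to 324. So 314 cannot fix a precise headroom, and a small allowance cannot be strictly excluded. That is fair. A material one would still have to show in the 50% row, and it does not.

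**The 80% belongs to 314.** A reader might infer that the plan promises 80% power at 300 and that any loss breaks the promise. The article does not say this. It attaches 80% to 314, and for 300 it gives only a detectable reduction. At 44%, a 5% loss alone leaves 77-78%, and smaller losses hardly matter.

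**The outcome is time to event over 24 months.** This is the strongest objection. If the one-year rates continue at a constant hazard (an assumption not in the article), the 24-month risks are 1 − 0.40² = 84% and 1 − 0.56² = 68.6%. A chi-squared test at 300 then has about 88% power with no loss (about 84% if the one-year experimental rate is 45%). A log-rank test has about 93% (90%). With 10% loss and 10% non-adherence the log-rank figure is about 84% (79%). The objection stands as a limit on the point. It does not repair the published justification, which uses one-year proportions only.

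**The scenarios are assumed.** They are, and giving non-adherers the full control rate is a worst case for those who stop partway. Home follow-up and counselling may keep both rates low.

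**Conclusion.** The point holds for the calculation that the article prints. The 25% and 50% rows of Table 1 are, to within rounding and choice of formula, complete-follow-up and full-adherence sizes, although the text attributes them to simulations of adherence and retention. Enrolling 300 leaves no margin at 44% and is short at a true 25% reduction. The statement that 300 corresponds to a reduction a little under 25% is wrong in direction: the figure is about 27%.

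The size of the shortfall depends on rates that the article does not give. At 44%, power falls to 73-74% with 5% loss and 5% non-adherence, and to 66-67% with 10% of each.

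A reader might go further and conclude that the 24-month trial is underpowered. The documents do not support that: these figures refer to a one-year two-proportion comparison, and a 24-month analysis could have considerably more power. Nor does the 10% row show that an allowance is absent, because it does not reproduce from its own printed rates.

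**What to change.** Keep the 300 patients and revise the Sample Size Calculation section as follows.

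1. Label the Table 1 sizes as assuming complete follow-up and full adherence, or state the adherence and retention inputs that the simulations used and show where they enter.
2. Replace the statement on the detectable reduction at 300 with the recomputed figure, about 27% on the one-year basis.
3. Give a small table of power at 300 over stated ranges of retention and selenium-arm adherence, for example 80-100% for each, and say that it refers to the one-year comparison.
4. If the 24-month time-to-event outcome is the intended basis, give the power for that outcome with its hazard, loss and adherence assumptions.

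The cost is some rewording and one recalculated table, with no added patients or procedures. The downside is that the stated one-year power becomes less favourable.
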